# A phase III randomized-controlled, single-blind trial to improve quality of life with stereotactic body radiotherapy for patients with painful bone metastases (ROBOMET)

**DOI:** 10.1186/s12885-019-6097-z

**Published:** 2019-09-04

**Keywords:** Stereotactic body radiotherapy, Bone metastases, Spinal metastases, Pain

## Abstract

**Background:**

Bone metastases represent an important source of morbidity in cancer patients, mostly due to severe pain. Radiotherapy is an established symptomatic treatment for painful bone metastases, however, when conventional techniques are used, the effectiveness is moderate. Stereotactic body radiotherapy (SBRT), delivering very high doses in a limited number of fractions in a highly conformal manner, could potentially be more effective and less toxic.

**Methods:**

This is a phase III, randomized-controlled, single-blind, multicenter study evaluating the response rate of antalgic radiotherapy for painful bone metastases and the acute toxicity associated with this treatment. A total of 126 patients will be randomly assigned to receive either the standard schedule of a single fraction of 8.0 Gy delivered through three-dimensional conformal radiotherapy or a single fraction of 20.0 Gy delivered through SBRT. Primary endpoint is pain response at the treated site at 1 month after radiotherapy. Secondary endpoints are pain flare at 24–48-72 h after radiotherapy, duration of pain response, re-irradiation need, acute toxicity, late toxicity, quality of life and subsequent serious skeletal events. In a supplementary analysis, patient-compliance for a paper-and-pencil questionnaire will be compared with an electronic mode.

**Discussion:**

If a dose-escalated approach within the context of single fraction stereotactic body radiotherapy could improve the pain response to radiotherapy and minimize acute toxicity, this would have an immediate impact on the quality of life for a large number of patients with advanced cancer. Potential disadvantages of this technique include increased pain flare or a higher incidence of radiation-induced fractures.

**Trial registration:**

The Ethics committee of the GZA Hospitals (B099201732915) approved this study on September 4th 2018. Trial registered on Clinicaltrials.gov (NCT03831243) on February 5th 2019.

## Background

Regrettably, a large proportion of cancer patients will ultimately develop systemic disease. Bone metastases are a common manifestation of distant relapse from many types of solid tumors, especially those arising in the lung, breast and prostate. They represent an important source of morbidity in these patients, mostly due to severe pain. Furthermore, they can cause hypercalcemia, pathologic fractures and spinal cord compression, all of which can significantly compromise quality of life. The goals of palliative radiotherapy of bone metastases are pain relief, preservation of function, and maintenance of skeletal integrity. Radiotherapy is an established symptomatic treatment for painful bone metastases. A common and convenient schedule uses a single dose of 8 Gy [1]. Several other fractionation schedules, using moderate dose escalation (5 × 4.0 Gy or 10-13 × 3.0 Gy), have been investigated. However, so far, none has demonstrated superiority to a single 8 Gy fraction [2]. A large meta-analysis by Rich et al. showed overall response rates of 61% versus 62% for single fraction and multiple fraction regimens [3]. Complete responses were seen in 23% versus 24% of patients. A drawback of single 8 Gy fraction treatment is a consistently higher retreatment rate (20% versus 8% in the meta-analysis). Retreatment gives moderate pain relief (overall pain response rates of 45–58%) regardless of prior response to palliative radiotherapy [4].

Palliative radiation therapy for bone metastases is usually performed using conventional or at most 3D-conformal radiotherapy (3D-CRT), rather than more advanced techniques such as intensity-modulated radiotherapy (IMRT). As a result, these palliative patients can sometimes suffer from rather pronounced acute toxicities, often during the last months of their lives. Stereotactic body radiotherapy (SBRT) is a recent state-of-the-art form of radiotherapy, typically delivering very high doses (> 6.0 Gy per fraction) in a limited number of fractions (1–5) in a highly conformal manner. This technique is safe due to corresponding improvements in image-guided radiotherapy (IGRT), allowing to continuously monitor the treatment as it is being delivered [5]. SBRT is able to deliver significantly higher biologically equivalent doses (BED) as compared to conventional radiation with improved sparing of surrounding normal tissues. It has consistently demonstrated local control rates of around 90%, even in “radioresistant” tumors [6]. Most studies on SBRT for bone metastases to date focused on so-called “oligometastatic” patients, with only a limited number of (usually asymptomatic) metastases, assuming that ablation of these lesions could result in improved disease-free and perhaps even overall survival [7]. While this is certainly a worth-wile approach, it seems reasonable to also use this technique for palliative patients suffering from painful bone metastases.

The highly conformal delivery of SBRT will hopefully result in an improved acute toxicity profile, based on the experiences captured in patient-reported rather than physician-reported measures. The concept of quality of life (QoL) is subjective; however, in many cancer cohorts, specific tools or patient-reported outcome measures (PROMs) have been developed and validated [8]. These questionnaires assess common issues that affect patients after diagnosis and treatment, and generate scores that reflect the impact on perceptions of health-related quality of life (HRQoL). A secondary aim of this study is to compare hand-written “paper” PROMs to electronic, “paper-less” PROMs.

Moreover, it is now possible to deliver escalated doses to the metastases. We propose a single fraction (avoiding the complexity of multiple fractions) of 20.0 Gy, which has a vastly superior BED compared to the previous (multiple fraction) dose-escalation attempts. It is to be assumed that with these truly “ablative” doses, not only a higher response rate can be achieved but also longer duration of pain control and less re-irradiation need. Perhaps this increased efficacy will compensate the higher treatment cost of SBRT, through less re-treatment and less symptomatic skeletal events (SSEs, consisting of symptomatic pathologic fractures, radiation or surgery to bone, and spinal cord compression).

## Methods/design

### Study design

This is a phase III, randomized-controlled, single-blind, multicenter study comparing the standard schedule for antalgic radiotherapy of a single fraction of 8.0 Gy delivered through 3D-CRT to a single fraction of 20.0 Gy delivered through SBRT (Fig. 1). The primary aim of this trial is to double the complete response rate. Secondary aims are to compare pain flare, duration of pain response, acute and late toxicity, HRQoL through PROMs, re-irradiation need and subsequent SSE.

**Fig. 1 Fig1:**
[figure not shown]
Study schema. Subjects who meet eligibility criteria and qualify for enrolment will be randomized as demonstrated

All subjects will be randomly assigned in a 1:1 ratio to receive either a single fraction of 8.0 Gy to the painful bone metastasis through 3D-CRT (control arm) or a single fraction of 20.0 Gy to the painful bone metastasis through SBRT (experimental arm). A block randomization with a block size of four will be performed by using an electronic randomization tool (Dyco Capture, DigiDyco).

This study has been approved by the Ethics Committee of GZA Hospitals and all collaborating institutions. All patients must provide written informed consent before enrolment. Monitoring will be carried out in this trial.

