### Eligibility criteria

Eligible patients are patients with a pain score ≥ 2 on a scale from 0 to 10 (measured as the worst pain for the previous 3 days at the index site), with radiological or (bone) scintigraphic evidence of bone metastasis at the site of pain and no more than 3 painful lesions needing treatment. If analgic dosing adjustment is done less than 1 week before initiation of irradiation, a run-in period is recommended to minimize the risk that the analgesic effects will confound the measurement of the RT effects. Patients should have a life expectancy estimated at > 3 months. Per lesion, no more than 3 consecutive spine segments should be involved, with one unaffected vertebral body above and below. Bone metastasis in previously irradiated sites, or originating from myeloma, or complicated bone metastasis, i.e. impending and/or existing pathological fracture, spinal cord compression or cauda equina compression [11], should be excluded.

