#### Target contouring

The gross tumor volume (GTV) will be delineated as visualized on CT. No clinical target volume (CTV) will be delineated in the experimental arm. In the standard arm standard CTV margins (e.g. incorporating the entire vertebra) are allowed. A planning target volume (PTV) will be created, allowing for daily set-up variance and organ motion. In the standard arm, PTV margins of 1 cm are common, in the experimental (SBRT) arm, PTV margins are 3 to 5 mm.

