#### Delivery and verification

In the standard arm, image-guidance will consist of portal images showing the relevant bony anatomy. For the experimental arm, treatment will be delivered with 6–18 MV photons of a linear accelerator with ESTRO-ACROP specifications for SBRT [12]. Image-guidance will consist of cone-beam CT in combination with 6 degrees of freedom corrections using robotic couch. No other RT than photon therapy is permitted. The same position and immobilization/support device(s) as used in the planning CT scan should be utilized. For the investigational arm, a pre-treatment patient-specific and treatment verification quality assurance (QA) program based on transmission dose measurements and cone-beam CT data will be performed.

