### Interventions

The screening procedures will determine subject eligibility according to inclusion and exclusion criteria. The following evaluation/assessments will be performed at the screening visit within 20 days of Day 1 (Table 2):
Obtain informed consentRecord the numeric pain rating scaleRecord the daily oral morphine equivalent (OMED) and other analgesicsRecord education level and computer experienceCollect details of disease and concurrent systemic anticancer treatmentECOG performance statusHRQoL questionnaires (and reason for non-compliance, if applicable)Toxicity (using the most recent version of CTCAE)

**Table 2 Tab2:** Trial flowchart

	Screening	Treatment					Follow-up
		Simulation	During study				Year 1
			RT	24–48-72 h	weekly	1 m	Every 3 m
Informed consent	x						
Registration of education level, computer experience^a^	x						
Randomization: 1 × 8.0 Gy 1 × 20.0 Gy		x					
Numeric Pain Rating Scale	x		x	x	x	x	x
ECOG performance status	x		x			x	
OMED + other analgesics	x		x	x	x	x	x
Registration of toxicity						x	x
Registration of QoL^b^	x					x	x
Registration of treatment data^c^			x				

^a^Education level:highest level of education (none, primary school, secundary school or higher education); computer experience: at least once a week access to computer/e-mail (yes or no)

^b^QoL according to the EORTC QLQ-C30 & BM22 questionnaires; if form is not completed, reason for non-compliance will be documented in compliance form

^c^See Section “Treatment compliance”

At Day 1, randomization and computed tomography (CT) simulation will be performed.

The following assessments must occur on the day of radiotherapy treatment (Table 2):
Record the numeric pain rating scaleRecord the daily oral morphine equivalent (OMED) and other analgesicsCollect RT dosing and delivery detailsECOG performance statusHRQoL questionnaires (and reason for non-compliance, if applicable)Toxicity (using the most recent version of CTCAE)

At 24 h, 48 h, 72 h, 1 week (+/− 3 days), 2 weeks (+/− 3 days) and 3 weeks (+/− 3 days) after RT subjects are asked to rate their pain flare and record concurrent medications in a pain diary.

The following procedures are to be conducted at primary endpoint visit (1 month after RT) and at each follow-up visit every 3 months up to 12 months (Table 2):

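### One fixed, published block size of four with unblinded treating staff makes allocation partly predictable: one in three assignments is certain if blocks are kept per centre, far fewer with one central list

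*Protocol article*

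**What the plan says.** The allocation rule is in the Study design section of the protocol article, after Fig. 1: "All subjects will be randomly assigned in a 1:1 ratio", and then "A block randomization with a block size of four will be performed by using an electronic randomization tool". No other block size is mentioned. The Data Availability section says that the trial was ongoing at publication, so the block size became public during the trial.

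The same section describes the trial: "This is a phase III, randomized-controlled, single-blind, multicenter study". It does not say who is blinded.

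Treatment differs visibly by arm. Under Target contouring: "No clinical target volume (CTV) will be delineated in the experimental arm", whereas the standard arm may use one. Under Delivery and verification: "In the standard arm, image-guidance will consist of portal images showing the relevant bony anatomy", whereas the experimental arm uses cone-beam CT with a robotic couch. Margins and linear accelerator requirements (Trial treatments) and beam arrangements (Treatment planning) differ too.

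On timing, the Interventions section says: "At Day 1, randomization and computed tomography (CT) simulation will be performed". Screening takes place within 20 days of that day.

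**The concern.** An electronic tool hides the next entry on the list but does not stop anyone deducing it. With every block of size four and two patients per arm, the fourth assignment follows from the first three. The third and fourth both follow from the first two when those are equal. The people who contour, plan and deliver treatment must know the arm, so single-blind cannot extend to them. That is an inference, but a firm one.

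If such knowledge reaches whoever decides on entry, there is room to act on it. One eligibility criterion is a judgement: "Patients should have a life expectancy estimated at > 3 months". The analgesic run-in is only recommended, and the screening window allows some choice of date. The primary endpoint depends on a self-rated pain score, entry needs a score of only 2 or more, and complete response needs a score of 0. Response can therefore depend on which patients enter each arm. Steering entry by expected arm would produce a difference between arms that is not due to treatment.

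**Working it through.** The article gives no figure for predictability, so there is none to reproduce. The sample size does not depend on this point.

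**Inputs.** Block size 4 and ratio 1:1 (Study design); 126 patients (Sample size calculation). The number of centres and their shares are not given, so the share s is an assumption and is shown over a range.

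**1. Certain assignments when every allocation in the block is seen** (blocks per centre, site tracks its list). There are 6 equally likely sequences of two and two.
- Positions 1 and 2: never certain.
- Position 3: certain if the first two are equal, probability 1/3.
- Position 4: always certain.
- Share certain = (0 + 0 + 1/3 + 1)/4 = 1/3 = 33.3%.

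For scale, a single fully observed list of 126 holds 31 complete blocks, and 31 × 4/3 ≈ 41 assignments are known in advance.

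**2. Best guess, same observer.** The rule is to guess the arm that is behind in the block and toss a coin when the arms are level. Probabilities of being right by position are 1/2, 2/3, 2/3 and 1. The mean is (1/2 + 2/3 + 2/3 + 1)/4 = 17/24 = 70.8%, against 50% for pure chance.

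**3. One central list, site with share s that sees only its own patients.** Assume that each place in a block goes to the site with probability s and that the site knows where blocks begin. The second assumption favours the site. The next arm is certain only if the site has itself seen both patients of the other arm.
- Position 3: the first two are equal (1/3) and both seen (s²), giving s²/3.
- Position 4: one arm is already complete, and both of its patients must have been seen, giving s².
- Share certain = (0 + 0 + s²/3 + s²)/4 = s²/3. Simulation agrees.

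| Site share s | Certain assignments (s²/3) |
|---|---|
| 1 | 33.3% |
| 0.75 | 18.8% |
| 0.50 | 8.3% |
| 1/3 | 3.7% |
| 0.25 | 2.1% |

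**4. Randomly varying block sizes, full list seen.** The observer knows the possible sizes but not which one comes next.
- Certain assignments, by simulation: about 2% with sizes 4, 6 and 8, and about 4% with sizes 2, 4 and 6.
- Best guess: the expected number of correct guesses in a block of 2k is k + ½(4^k / C(2k,k) − 1). This gives 1.5, 2.833, 4.1 and 5.329 for sizes 2, 4, 6 and 8.
- Sizes 4, 6 and 8, equally likely: (2.833 + 4.1 + 5.329)/(4 + 6 + 8) = 12.262/18 = 68.1%.
- Sizes 2, 4 and 6: (1.5 + 2.833 + 4.1)/(2 + 4 + 6) = 8.433/12 = 70.3%.
- A block of two alone: 1.5/2 = 75%, the most guessable size.

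**The case against.** The strongest objection is that one in three is a worst case. The article describes one block randomisation through one electronic tool and mentions neither lists per centre nor stratification, so a central list is at least as natural a reading. A site seeing only its own patients would then know far less. This stands. A reader might infer that any participating site can know a third of its assignments, but the article does not support that without the list structure.

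Nor does the article say who screens, consents and enters patients. That the staff who learn the allocations also enrol is likely in radiotherapy practice, but it is not stated. A reader might go further and infer that the trial is biased. Nothing in the document shows steering, and any figure for bias in the response rate would need an assumed steering effect.

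The silence on list structure and concealment is not itself an error, since a journal article commonly leaves these to the full protocol.

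On the remedy, varying the block size hardly affects guessing, because the arms are level at the end of every block whatever its size. This also stands: the gain is in removing certainty. A reader might also conclude that lists per centre should be introduced. If the present list is central, that would let each site see a complete list and could raise predictability.

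What the objections do not remove is the stated rule. A single small block size, disclosed during enrolment in a trial whose treating staff know each allocation, is predictable to a degree that costs almost nothing to reduce.

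**Conclusion.** The point holds conditionally. With blocks per centre and a site that tracks its allocations, 33% of assignments are certain and 71% can be guessed. With a central list, a site seeing only its own share s is certain of about s²/3, or 8% at one half and 2% at one quarter. Which case applies cannot be settled from the article.

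The conclusion rests on one firm inference, that treating staff know the arm, and on one open premise, that this knowledge can reach whoever decides on entry. Selection bias is therefore a risk that the design leaves open and not something shown to occur. This is an avoidable weakness that should be corrected while patients remain to be randomised. It is not a fatal flaw.

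**What to change.** For patients not yet randomised, keep the existing list structure, central or per centre, and generate the remaining list with randomly varying block sizes. Leave out blocks of two; 4, 6 and 8 would serve. Hold the sizes in the randomisation tool and do not disclose them to sites or in publications until enrolment ends. The size of four already published cannot be withdrawn, but it would no longer describe the remaining list.

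With the full list seen, certain assignments fall from 33% to about 2%, and best-guess accuracy falls only from 71% to about 68%.

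The cost is a new list in the existing tool and a slightly larger possible imbalance where a list stops mid-block. The maximum is half the block size, so it rises from 2 patients to 4 with blocks of up to 8. Sample size and endpoints do not change.

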### Study objectives

#### Primary endpoint

Primary endpoint of this study is pain response at the treated index site at 1 month after RT, as defined according to the International Bone Metastases Consensus Endpoints for Clinical Trials (Table 1) [9].

**Table 1 Tab1:** Response rate to radiotherapy according to the international consensus [9]

Complete response	Pain score of 0 at the treated site and stable or reduced analgesics in daily oral morphine equivalent (OMED).
Partial response	Pain reduction of 2 or more at the treated site on a scale of 0 to 10 scale without analgesic increase, or analgesic reduction of 25% or more from baseline without an increase in pain.
Pain progression	Increase in pain score of 2 or more above baseline at the treated site with stable OMED, or an increase of 25% or more in OMED compared with baseline with the pain score stable or 1 point above baseline
Indeterminate response	Any response that is not captured by the complete response, partial response, or pain progression definitions

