#### Secondary endpoints

Secondary endpoints include pain flare at 24–48-72 h after radiotherapy, the duration of pain response, re-irradiation need, toxicity, HRQoL and subsequent SSE. Pain flare at 24–48-72 h after radiotherapy is defined as pain progression according to the consensus statement [9]. Duration of pain response starts at response until pain progression. Toxicity will be measured with the Common Terminology Criteria for Adverse Events (CTCAE) version 5.0 at 1 month after RT and three-monthly during the first year after treatment. HRQoL is measured by the EORTC QLQ-C30 general questionnaire and the bone metastasis-specific module, the EORTC QLQ-BM22 [10]. Patients fill out these questionnaires before the start of RT (baseline), 1 month after RT (primary endpoint) and three-monthly during the first year after treatment (follow-up). Subsequent SSE is defined as symptomatic pathologic fractures, radiation or surgery to bone, and spinal cord compression.

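### Table 1 classes a patient who worsens on both pain and OMED as indeterminate, although worsening on either alone is progression, so pain flare can be under-counted and response duration overstated

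*Protocol article*

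**What the plan says.** Table 1 (Study objectives, Primary endpoint) is captioned "Response rate to radiotherapy according to the international consensus". Its pain progression row has two limbs:

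- Limb 1: "Increase in pain score of 2 or more above baseline at the treated site with stable OMED".
- Limb 2: "an increase of 25% or more in OMED compared with baseline with the pain score stable or 1 point above baseline".

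The last row, indeterminate response, takes "Any response that is not captured by the complete response, partial response, or pain progression definitions".

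The Secondary endpoints section applies progression to two further outcomes. Pain flare at 24, 48 and 72 h "is defined as pain progression according to the consensus statement", and "Duration of pain response starts at response until pain progression". Neither has a separate rule for pain and analgesic use rising together.

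Both components are collected. Table 2 schedules the pain scale and OMED at 24–48–72 h, weekly, at 1 month and every 3 months, and under Interventions "subjects are asked to rate their pain flare and record concurrent medications in a pain diary".

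**The concern.** Each limb restricts the other scale: limb 1 needs OMED to be stable, and limb 2 needs pain to be no more than 1 point up. Nothing covers the patient who crosses both thresholds at once. That patient is worse on both axes, yet receives a more favourable label than a patient who is worse on one.

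This matters most for flare. A patient in more pain in the first three days can plausibly take more opioid, so combined rises are not a remote case. Flare is also one of the harms the trial sets out to compare. The abstract states: "Potential disadvantages of this technique include increased pain flare or a higher incidence of radiation-induced fractures". For duration of response, a responder who relapses on both scales has not formally progressed at that visit, so the recorded duration runs on.

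**Working it through.** **Step 1. Apply Table 1 literally.** Changes are from baseline. *Stable* OMED is not defined in the table, so two readings are tried: no change at all, or a change of less than 25%.

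| Pain change | OMED change | Limb 1 | Limb 2 | Class |
|---|---|---|---|---|
| +2 | 0 | met | not met | progression |
| +4 | 0 | met | not met | progression |
| 0 | +25% | not met | met | progression |
| +1 | +50% | not met | met | progression |
| +2 | +25% | not met | not met | **indeterminate** |
| +4 | +50% | not met | not met | **indeterminate** |
| +2 | +10% | depends on *stable* | not met | progression or indeterminate |

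The two bold rows come out the same under either reading of *stable*. The gap therefore follows from the wording and needs no assumed number. The last row is a smaller ambiguity from the same undefined term.

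**Step 2. Check what is not affected.** Pain up by 2 or more rules out complete response (pain score 0). With OMED also up, it rules out partial response too, since that needs lower pain without an analgesic increase, or lower analgesic use without more pain. Such a patient is a non-responder at 1 month whichever label applies. The sample size rests on complete response of 25% vs 50% with type I error 0.05 and power 0.8. Taking the test as two-sided, n per arm = [1.96·√(2·0.375·0.625) + 0.842·√(0.25·0.75 + 0.50·0.50)]² / 0.25² = 57.7, so 58 per arm, or 116. This reproduces the stated figure, and nothing in it depends on the progression rule.

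**Step 3. Illustrate the possible size for flare.** The protocol gives no flare calculation to reproduce. Inputs:

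- n = 63 per arm: 126 patients, allocated 1:1, with no drop-out applied.
- True flare after 3D-CRT 40%: the approximate figure in the Discussion.
- True flare after SBRT 60%: **assumed**, within the 10–68% range in the Discussion.
- Share f of flares lost to the gap: **assumed** equal in both arms, 20% to 50%. The documents give no figure.

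Observed rate = true rate × (1 − f), so the absolute difference also shrinks by (1 − f).

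Power = Φ{(|p₂ − p₁| − 1.96·s₀)/s₁}, with s₀ = √(2p̄(1 − p̄)/n) and s₁ = √([p₁(1 − p₁) + p₂(1 − p₂)]/n).

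| f | Observed rates | Difference | s₀ | s₁ | Power |
|---|---|---|---|---|---|
| 0 | 40% vs 60% | 20 points | 0.0891 | 0.0873 | Φ(0.29) = 61% |
| 20% | 32% vs 48% | 16 points | 0.0873 | 0.0861 | Φ(−0.13) = 45% |
| 30% | 28% vs 42% | 14 points | 0.0850 | 0.0841 | Φ(−0.32) = 38% |
| 50% | 20% vs 30% | 10 points | 0.0772 | 0.0766 | Φ(−0.67) = 25% |

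If no patient ever has both rises, f = 0 and the rule does no harm. If the true flare rates are equal in the two arms, an equal loss creates no false difference; it only lowers both rates.

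**The case against.** **The rule is an adopted standard.** Table 1 is presented as the international consensus, and flare is defined by reference to that consensus. The source cannot be checked here, so the gap may be inherited, or may have arisen when the table was condensed. Departing from a shared rule also costs comparability, and the Discussion itself lists inconsistent flare definitions as a reason why studies are hard to compare. The comparability point stands and shapes the fix. It does not remove the defect: the table is printed as the trial's own classification, and its residual row explicitly sends these patients to indeterminate. If the source does cover combined rises, Table 1 needs correcting for that reason instead.

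**A patient missed once may be caught later.** Flare is assessed three times. If meeting the rule at any one of them suffices, a patient counts who has pain up by 2 before the opioid rises, or whose pain settles to 0 or 1 point above baseline on more opioid. This stands. The loss applies only to patients who meet neither limb at every assessment, and f may be well below the illustrated range.

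**Flare is secondary and carries no power target.** Also true. On the assumed rates, power is only 61% before any loss, so the power figures show direction and scale and are not a failed design target.

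**The data permit a broader rule later.** They do, but choosing the rule for a harm endpoint after seeing the data is weaker than fixing it beforehand.

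**Conclusion.** The point holds as a defect of classification. Table 1 labels simultaneous worsening on pain and OMED as indeterminate while worsening on either alone is progression, and the protocol carries that rule into pain flare and the end of response duration. Flare can be under-counted and duration overstated, in both arms. Complete response and the sample size are untouched.

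The size of the effect cannot be derived from the documents. The drop from 20 to 16–10 points, and from 61% to 45–25% power, rests on an assumed 60% SBRT rate and an assumed equal loss of 20% to 50%.

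A reader might infer three stronger conclusions that the documents do not support:

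- *The rule drops the worst flares.* Not necessarily: pain up by 6 on stable OMED is counted, while pain up by 2 with OMED up by 25% is not.
- *The rule hides an SBRT harm.* That needs combined rises to be commoner after SBRT. Losing 30% of control flares and 50% of SBRT flares would give 28% vs 30%, but nothing in the protocol supports such a split. The quoted SBRT range of 10–68% lies on both sides of the 40% for 3D-CRT, so even the direction of the true difference is open.
- *Flare is the main acute harm of SBRT.* The protocol calls it a potential disadvantage, alongside fractures.

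**What to change.** For pain flare and for the end of response duration, define progression as either:

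- pain up by 2 or more from baseline with OMED stable **or increased**; or
- OMED up by 25% or more from baseline with pain stable **or increased**.

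This also settles the case of pain up by 2 with a small OMED rise, whichever meaning *stable* has. Report flare and duration under the literal Table 1 wording as a sensitivity analysis, and make the change before the data are analysed.

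The cost is one line of definition and one extra table. Pain and OMED are already scheduled at every relevant time point, so no new data are needed and the sample size does not change. The small downside is that the main flare and duration results become slightly less directly comparable with studies that use the literal wording; the sensitivity analysis covers this.
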